### Intervention

Human pharmacokinetic data indicate a linear relationship between dose and plasma peak concentration. Continuous infusion at higher daily doses is required to sustain plasma levels considered necessary for antioxidant and endothelial effects (19). Our preliminary data revealed a critical dose–response discrepancy: while a dosage of 200 mg/kg effectively improved inflammatory biomarkers in patients with MSAP, no comparable clinical benefit was observed in the SAP cohort (6). This divergence suggests that SAP represents a catastrophic ‘Redox Storm’, where the production of ROS exponentially overwhelms the neutralizing capacity of conventional regimens. Vitamin C exhibits a linear dose-concentration relationship in critically ill patients. Continuous infusion provides stable steady-state plasma concentrations proportional to the daily dose (20). Notably, a comprehensive scoping review has validated the safety of ultra-high-dose intravenous vitamin C, reporting an average well-tolerated dosage of 455 mg/kg/d (ranging from 260 to 925 mg/kg/d) across critically ill and oncological populations (21). Guided by this safety benchmark of 455 mg/kg/d, we have escalated our study dose to 500 mg/kg per 24 h (administered from 06:00 to 06:00 the following day) for 7 consecutive days, aiming to surpass the therapeutic threshold and capture a definitive treatment effect in SAP.

To ensure pharmacological consistency across centers, the study medication is standardized. Vitamin C is sourced from a single manufacturer (Chengdu Brilliant Pharmaceutical Co., Ltd., Chengdu, China; National Medicine Permission Number: H32022732) from one production batch. The medication is supplied in ampoules of 1 g per 5 mL (200 mg/mL). The solvent is water for injection, with sodium metabisulfite, cysteine hydrochloride, disodium edetate, and anhydrous sodium carbonate as excipients. To avoid fluid overload in SAP patients, vitamin C is given as the undiluted original solution. For the intervention group, the weight-based dose (500 mg/kg/day) is drawn into 50 mL light-proof syringes by an unblinded drug preparation nurse (UDPN). The solution is administered continuously via a central venous catheter using a micro-infusion pump at 2 g/h. The control group receives 0.9% normal saline at 10 mL/h to match the vitamin C infusion, for a daily sodium chloride load of approximately 2.16 g. Throughout the intervention period, patients will be closely monitored for adverse effects. If complications such as cystinuria, gout, hyperoxaluria, oxalate deposition, or urate kidney stones occur, the dosage should be adjusted as clinically indicated. In severe cases, the trial may be discontinued.

During the intervention, if an interruption occurs (such as CT transport, infusion pump disconnection, central line failure) the infusion will be temporarily paused and later resumed at the identical constant rate of 2 g/h. Catch-up boluses or rate increases are prohibited. Interruptions under 2 h per 24-h cycle are considered acceptable. Longer interruptions are documented as protocol deviations but the patient remains in the study under ITT analysis.

Vitamin C has low molecular weight and high water solubility, so it is cleared during CRRT. The baseline dose is high enough that plasma levels should stay well above the therapeutic threshold even during continuous renal replacement therapy (CRRT). Keeping the dose unchanged avoids rebound toxicity risk if CRRT is interrupted unexpectedly, and it keeps the protocol consistent across all study centers. We will document CRRT parameters (duration, modality, effluent dose) in Table 1 and include them in statistical adjustments and subgroup analyses to capture how CRRT affects drug exposure.

**Table 1 tab1:** Collected procedures, data, and outcomes.

Procedures	Day 0	Day 1	Day 3	Day 7	Day 14	Day 28	Day 180
Eligible criteria	x						
Informed consent	x						
Demographic and medical data	x						
Vital signs	x	x	x	x	x	x	
Laboratory biomarkers^*^	x	x	x	x	x	x	
Plasma vitamin C concentration	x	x	x	x			
SOFA score	x	x	x	x	x	x	
APACHE II score	x	x	x	x	x	x	
Antibiotics							
Surgical intervention							
Continuous renal replacement therapy (modalities, durations, and intensities)	x	x	x	x	x	x	
Mechanical ventilation	x	x	x	x	x	x	
Vasoactive drugs	x	x	x	x	x	x	
Gut microbiota	x	x	x	x	x	x	
Fluid retention^#^							
Abdominal CT scan	x			x	x	x	
Death							x
Hospital stay							x

CT, computed tomography; SOFA, sequential organ failure assessment; APACHE II, acute physiology and chronic health evaluation II.

* Laboratory biomarkers include: blood cell analysis, blood gas analysis, C-reactive protein, procalcitonin, coagulation test, liver function, renal function, NT-proBNP, TnI, cytokines, immunoglobulin, pancreatic enzymes.

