**Method:**

This is a prospective, randomized, double-blind, multicenter clinical trial. Participants will be stratified and randomly assigned to either the HDIVC group or the control group. Data will be analyzed using SAS 9.4 with two-sided tests and a significance threshold of *p* < 0.05. This study will be conduct at eight hospitals in China, including Shanghai Jiao Tong University School of Medicine Affiliated Ruijin Hospital, Shanghai General Hospital, Changhai Hospital, Sichuan Provincial People’s Hospital, Chongqing Daping Hospital, The Second People’s Hospital of Chengdu, Guanghan People’s Hospital and Chongqing Emergency Medical Center. Eligible patients are adults (age ≥ 18 years) diagnosed with severe acute pancreatitis according to 2012 Atlanta classification within 7 days of onset. HDIVC (500 mg/kg, 2 g/h) or placebo (normal saline) will be administered via central vein for 7 days. The primary outcome is organ support-free days within the first 14 days. Secondary outcomes include ICU all-cause mortality, changes in inflammatory biomarkers, and organ failure scores.

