In our preclinical work, vitamin C supplementation lowered inflammatory markers, mortality, and pancreatic necrosis in SAP mice (15, 16). Whether this carries over to humans is unclear. Existing clinical data are inconsistent and come from small samples, insufficient dosing, or cohorts weighted toward mild disease (17). From September 2019 to December 2023, we conducted a single-center, double-blind, randomized, placebo-controlled trial (ChiCTR1900022022) investigating HDIVC (200 mg/kg/24 h, 1 g/h, for 7 days) (6). The primary outcome of 28-day mortality did not differ significantly between treatment groups in the overall cohort (*n* = 212). However, prespecified subgroup analysis revealed that MSAP patients receiving HDIVC demonstrated significant reductions in C-reactive protein levels and improved fluid balance. These findings suggest HDIVC may attenuate inflammatory responses in MSAP, though its therapeutic value in SAP requires confirmation through adequately powered multicenter randomized controlled trials. Extensive preclinical investigations over the past few decades have established the therapeutic potential of HDIVC in SAP, with mechanistic understanding progressively refined through cellular, animal, and early-phase human studies. While these foundational studies show biological plausibility, current clinical evidence remains limited to underpowered single-center trials, precluding definitive conclusions about therapeutic efficacy. To address this critical evidence gap, we propose a multicenter, prospective, randomized, double-blind, placebo-controlled trial evaluating early HDIVC administration (500 mg/kg/day for 7 days, 2 g/h) in SAP patients. The primary outcome is organ support-free days (OSFD) within the first 14 days. Secondary outcomes include ICU all-cause mortality, inflammatory biomarker, organ failure scores and fluid retention. This study aims to determine whether HDIVC represents a clinically meaningful, cost-effective therapeutic intervention capable of improving outcomes in this high-mortality condition, with potential to inform future guideline recommendations.

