#### Exclusion criteria

Participants who meet any of the following criteria will be excluded from the study:

SAP caused by tumors or ERCP;Pregnancy or breastfeeding;Allergy to vitamin C;Use of other experimental drugs during the study period;Pre-existing chronic organ failure affecting the heart, liver, lung, or kidney prior to admission, defined as: chronic cardiovascular dysfunction requiring long-term mechanical hemodynamic support or inotropic drugs; chronic obstructive pulmonary disease requiring home oxygen therapy; chronic liver failure classified as Child-Pugh grade C; chronic kidney disease defined by eGFR less than 60 mL/min/1.73 m^2^ (CKD-EPI 2021). Baseline creatinine is based on stable outpatient values from the past 6 months; if unavailable, exclusion relies on a documented history of chronic kidney disease rather than an acute admission creatinine.Immunosuppressive states, including malignant tumors, post-transplant conditions, long-term use of immunosuppressor (for at least 1 month before enrollment), or AIDS;Refuse to sign the informed consent form;Weight > 100 kg;Presence of urinary tract stones identified during the current admission (including symptomatic clinical events or incidental findings on baseline abdominal imaging).Known personal or strong family medical history of G6PD deficiency (routine laboratory screening is not required prior to enrollment).

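### A dose of 500 mg/kg per 24 h and a fixed continuous 2 g/h agree only at 96 kg: below that weight the dose runs out early, and above it the dose cannot be finished

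*Protocol article*

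**What the plan says.** The Intervention section of the Protocol article gives the daily dose as "500 mg/kg per 24 h (administered from 06:00 to 06:00 the following day) for 7 consecutive days". For preparation, "the weight-based dose (500 mg/kg/day) is drawn into 50 mL light-proof syringes", using undiluted solution at 200 mg/mL. For delivery, "The solution is administered continuously via a central venous catheter using a micro-infusion pump at 2 g/h". After a pause, "the infusion will be temporarily paused and later resumed at the identical constant rate of 2 g/h", and the rate may not be raised to catch up. The abstract repeats the pairing: "HDIVC (500 mg/kg, 2 g/h) or placebo (normal saline) will be administered via central vein for 7 days".

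Control patients receive 0.9% saline at 10 mL/h, said to match the active infusion, with a stated daily sodium chloride load of about 2.16 g. The section on randomization and blinding requires equal volumes and identical administration in both arms.

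The only weight limit is the exclusion "Weight > 100 kg", and the Discussion mentions a cap of 50 g per day. Nowhere is 2 g/h described as a maximum, scaled to weight, or given a stop time.

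**The concern.** A daily dose that scales with weight, a fixed 24-h window and a fixed hourly rate cannot all hold except at one weight. The site must give up one of them, and the text does not say which.

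The choice matters because the infusion pattern is part of the hypothesis. The Intervention section argues that "Continuous infusion provides stable steady-state plasma concentrations proportional to the daily dose". The Discussion sets this trial apart from earlier negative trials partly because it uses continuous pump infusion with stable levels rather than bolus injection. If the infusion stops for hours each day in lighter patients, the result does not cleanly test that regimen. It also breaks the proportionality argument: at a fixed 2 g/h a larger daily dose lengthens the run but does not raise the rate. If the pump runs for the full 24 h instead, the dose per kilogram rises as weight falls.

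The placebo is affected too. Saline run for 24 h beside an active infusion that ends early would give the arms different volumes and pump times, which is a visible cue to allocation.

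**Working it through.** **Inputs (Protocol article).** Dose 0.5 g/kg per 24 h; rate 2 g/h; concentration 0.2 g/mL; saline 0.9% (0.009 g/mL) at 10 mL/h (all Intervention); maximum weight 100 kg (Exclusion criteria). The article gives no weight distribution, so the weights below are illustrative.

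**The plan's own figure.** 10 mL/h × 24 h × 0.009 g/mL = 2.16 g sodium chloride. This reproduces the stated load, so the matched infusion is written as a full 24-h run of 240 mL. The rates also agree: 2 g/h ÷ 0.2 g/mL = 10 mL/h.

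**Weight at which dose and rate agree.** 2 g/h × 24 h = 48 g; 48 ÷ 0.5 = 96 kg.

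**Other weights.**
- Run-time at 2 g/h = 0.5 × kg ÷ 2 = kg/4 hours; time off = 24 − kg/4.
- Rate while running = 2000/kg mg/kg/h, against 500/24 = 20.8 mg/kg/h if spread evenly.
- Dose if run for 24 h = 48,000/kg mg/kg.
- Matched saline = 2.5 mL/kg, or 2.5 × 0.009 = 0.0225 g sodium chloride per kg.

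| Weight | Daily dose | Run-time | Off per day | mg/kg/h while running | mg/kg/d if run 24 h | Matched saline (NaCl) |
|---|---|---|---|---|---|---|
| 50 kg | 25 g | 12.5 h | 11.5 h (48%) | 40.0 | 960 | 125 mL (1.13 g) |
| 60 kg | 30 g | 15 h | 9 h (38%) | 33.3 | 800 | 150 mL (1.35 g) |
| 70 kg | 35 g | 17.5 h | 6.5 h (27%) | 28.6 | 686 | 175 mL (1.58 g) |
| 80 kg | 40 g | 20 h | 4 h (17%) | 25.0 | 600 | 200 mL (1.80 g) |
| 96 kg | 48 g | 24 h | 0 | 20.8 | 500 | 240 mL (2.16 g) |

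**Above 96 kg.** At 100 kg, 50 g ÷ 2 g/h = 25 h. In 24 h the patient gets 48 g, or 480 mg/kg, which is 4% short. A tolerated pause of nearly 2 h with no catch-up leaves about 22 h × 2 g/h = 44 g, so on such a day the dose cannot be finished above about 44 ÷ 0.5 = 88 kg.

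**24-h run against the cited safety range.** The Intervention section cites doses up to 925 mg/kg/d. A 24-h run exceeds this below 48,000 ÷ 925 ≈ 52 kg.

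**Earlier trial.** The Introduction describes the earlier regimen in the same form, "200 mg/kg/24 h, 1 g/h, for 7 days". There 1 g/h × 24 h = 24 g, and 24 ÷ 0.2 = 120 kg. Both regimens pair a dose with a rate that fit at a single high weight, which suggests that in practice the pump runs until the dose is used up.

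**The case against.** Up to 96 kg a site can respect both the daily dose and the rate by drawing up 500 mg/kg and running it at 2 g/h until empty. The 06:00-to-06:00 wording may only define the dosing cycle. On this reading the total dose is right, and the 600 to 960 mg/kg figures do not arise, since they would need more drug than is drawn up. A 15- to 20-h infusion is still not a bolus, and the article gives no half-life from which to judge how far levels fall in the off-hours. Training and competency checks may already have fixed one reading. The blinding risk arises only if sites break the equal-volume rule. Above 96 kg the shortfall is small, and a 50 g cap need not be reached.

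Much of this stands. Run-until-empty is the likelier reading, the higher doses are the less likely case, the unblinding risk is conditional, and the effect above 96 kg is minor. But run-until-empty does not reconcile the text. It conflicts with continuous delivery, with the steady-state rationale and with a placebo load that can only come from 24 h at 10 mL/h. If saline really runs for 24 h, it also conflicts with equal volumes in the two arms. Nor is this detail that an article leaves to a fuller protocol: the figures it does state disagree with one another.

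**Conclusion.** The concern holds and must be fixed. As written, dose, window and rate agree at 96 kg and at no other eligible weight. On the likelier reading the total dose is correct up to 96 kg, but the infusion is off for 17% of the day at 80 kg, 27% at 70 kg, 38% at 60 kg and 48% at 50 kg. On the less likely reading the dose per kilogram is 20% too high at 80 kg (600/500) and 92% too high at 50 kg (960/500). Above 96 kg the shortfall is at most 4% in an uninterrupted 24 h.

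The arithmetic uses only the article's figures. How many patients are affected, and how far, depends on their weights, which are not reported. The fall in plasma level during the off-hours is not estimated here. The type I error rate, the sample size and the validity of the randomised comparison are untouched. What is in doubt is which regimen that comparison tests.

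**What to change.** Preferred: replace 2 g/h throughout, including the abstract, the blinding section and the rule for resuming after a pause, with a weight-based rate of 500 mg/kg over 24 h. That is 20.83 mg/kg/h; divided by 200 mg/mL it is about 0.104 mL/kg/h, or 5.2 mL/h at 50 kg, 6.3 at 60 kg, 7.3 at 70 kg, 8.3 at 80 kg and 10.4 at 100 kg.

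Alternative: keep 2 g/h, state the stop time as weight/4 hours with a ceiling of 48 g above 96 kg, and withdraw the claim of continuous steady-state delivery. A flat 48 g per day for everyone should not be adopted, because it gives lighter patients more per kilogram.

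Under either option:
- Give saline at the same patient-specific rate, volume and run-time, and replace the 2.16 g load with weight × 0.0225 g (1.58 g at 70 kg). Under the alternative, the 48 g ceiling holds this at 2.16 g above 96 kg.
- State that the 50 mL in the blinding section is the volume per syringe.
- Add stop time and volume given to the infusion record listed under Monitoring.
- Establish what the 34 patients already recruited received.

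The cost is a protocol amendment with ethics review, a rate or stop-time table by weight, and retraining of the drug-preparation nurses. No extra patients are needed. If earlier and later patients received different regimens, the report must describe this.

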### Primary outcome

This study assesses the effect of HDIVC on organ support-free days (OSFD) within the first 14 days in SAP patients. OSFD refers to the number of days a patient does not require circulatory support (vasoactive agents), respiratory support (mechanical ventilation), or renal support (renal replacement therapy). For patients who die within the 14-day observation period, OSFD is assigned a value of 0 day.

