### Data collection and management

To accurately capture the true severity and clinical heterogeneity of severe acute pancreatitis, comprehensive baseline and dynamic clinical parameters will be systematically recorded in the electronic Case Report Forms (eCRF). These explicitly include: (1) pancreatic enzyme levels over time; (2) daily APACHE II and SOFA scores; (3) the exact degree of extrapancreatic organ involvement and specific organ failures (e.g., respiratory, cardiovascular, and renal impairment); and (4) the requirement and duration of advanced therapeutic interventions, specifically including mechanical respiratory support, hemodynamic support (vasopressors), and CRRT. Recording these decisive clinical variables ensures a rigorous evaluation of the true therapeutic value of HDIVC in the overall care of SAP. Missing data for the primary and secondary outcomes will be addressed using multiple imputation by chained equations (MICE), assuming the data are missing at random. If not, last observation carried forward (LOCF) will be used. Source documents will be maintained for verification. The database will be locked after monitoring and queries resolution for final analysis.

Fecal samples will be collected within 24 h of enrollment (baseline), on treatment Day 7, and on Day 14. Samples will be frozen at −80 °C and shipped to the central laboratory. Total genomic DNA will be extracted, and the V3–V4 hypervariable region of the 16S rRNA gene will be PCR-amplified and sequenced by a certified sequencing service provider.

To minimize inter-center variability, concomitant treatments such as fluid resuscitation and antibiotic use will be guided by the same recommendations for severe acute pancreatitis management (21). Although minor variations reflecting local practice are expected, adherence to a standardized framework will be reinforced through investigator training and regular monitoring. All concomitant therapies will be prospectively recorded, and potential confounding effects will be addressed through statistical adjustment in the final analysis. Center will be included as a random intercept in the primary mixed-effects model to account for clustering of patients within centers.

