### Monitoring

All investigators (physicians, UDPNs, nurses, pharmacists, and data managers) must complete standardized training and pass a competency assessment before center activation. Study medication originates from a single production batch across all eight centers to ensure pharmacological consistency.

Adherence to the infusion protocol is monitored daily. Study nurses record infusion start time, rate, interruptions, and interruption causes in the electronic CRF. Cumulative interruptions <2 h per 24-h cycle are considered acceptable and interruptions ≥2 h are classified as protocol deviations, with the patient retained in the ITT analysis.

Each center’s PI reviews deviations quarterly and submits summary reports to the DMC. If the deviation rate for any procedure exceeds 10% at a given center, targeted retraining is initiated. The DMC reviews cross-center deviation patterns regularly. Systematic inter-center differences trigger focused quality assurance measures.

A combined approach of central statistical monitoring and periodic on-site monitoring is employed. Concomitant therapies (fluid resuscitation, antibiotics, nutritional support) follow standardized SAP management guidelines across all centers, and all such therapies are prospectively recorded for potential statistical adjustment.

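### Planned adjustment for, and subgrouping by, CRRT received after randomisation (and adjustment for concomitant therapy) conditions on part of the primary outcome and conflicts with the stated primary model and subgroup list

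*Protocol article*

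**What the plan says.** All places are in the protocol article.

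- **Intervention (CRRT paragraph):** the trial will record CRRT duration, modality and effluent dose and "include them in statistical adjustments and subgroup analyses to capture how CRRT affects drug exposure".
- **Table 1:** the row "Continuous renal replacement therapy (modalities, durations, and intensities" is marked on Days 0, 1, 3, 7, 14 and 28.
- **Primary outcome:** a day counts towards OSFD only if it is free of vasoactive drugs, "respiratory support (mechanical ventilation), or renal support (renal replacement therapy"). A patient who dies within 14 days scores 0.
- **Data collection and management:** after stating that all concomitant therapies are recorded, "potential confounding effects will be addressed through statistical adjustment in the final analysis".
- **Monitoring**, on fluids, antibiotics and nutrition, is softer: "all such therapies are prospectively recorded for potential statistical adjustment".
- **Statistical methods:** the primary analysis of OSFD is a linear mixed model with a random intercept for centre. No CRRT or therapy covariate is named, and the listed sensitivity analyses vary only the handling of centre. Prespecified subgroups are those of disease severity and baseline features, examined by interaction tests.

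**The concern.** CRRT duration and delivered effluent dose accumulate during follow-up, so apart from what is already running on Day 0 they can be consequences of the assigned treatment. The protocol gives reasons to expect an effect either way: Expected results anticipates that the drug halts progression to multiple organ failure, while the safety sections watch for acute kidney injury and oxalate nephropathy.

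A CRRT day is also, by definition, a day lost from OSFD. A between-arm model for OSFD containing CRRT days therefore holds fixed part of what it is meant to compare. Subgroups formed by later CRRT use have the same fault, because membership may depend on treatment and the arms within a subgroup are no longer randomised groups.

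Concomitant therapies given after randomisation are not confounders of a randomised comparison; they may lie on the causal path. One secondary outcome shows this directly: fluid retention is computed partly from intravenous fluids and enteral nutrition, which overlap with the fluid and nutritional therapies recorded for possible adjustment.

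At stake is whether a reported effect is still the effect of assignment to vitamin C. The most serious case is a renal harm that adjustment makes disappear.

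**Working it through.** **1. The plan's own figure.** Inputs from Sample size: difference 2 days, SD 5, two-sided alpha 0.05, power 0.80.

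n per group = 2 × (5 × (1.960 + 0.842) / 2)² = 98.1; the plan states 98. Then 98 × 1.15 = 112.7, so 113; 113 / 0.95 = 118.9, so 119; 2 × 119 = 238. The plan's figures are reproduced, and the calculation contains no CRRT or therapy covariate.

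**2. The sections side by side.**

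| Question | Intervention; Data collection and management; Monitoring | Statistical methods |
|---|---|---|
| Covariates | CRRT parameters; concomitant therapies (only possible in Monitoring) | Centre only, for the primary model |
| Subgroups | CRRT parameters | Severity and baseline features |
| Limited to Day 0 values? | Not stated | Baseline, for subgroups other than severity |
| Limited to a concentration model? | Not stated | Not stated |

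The two columns cannot both govern the efficacy analyses.

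**3. Direction and possible size of the distortion (illustrative).** The documents give no CRRT rates, so every input here is an assumption: 20% mortality unaffected by treatment; circulatory, respiratory and renal support durations centred on 4, 6 and 5 days in controls with SD 3.5, rounded and cut to 0–14; CRRT days not cut short at death; OSFD = 14 minus the longest duration, or 0 if dead; shared unmeasured severity either absent or strong (3 days of duration per SD of severity). There were 400,000 patients per scenario. Least squares of OSFD was fitted on arm alone, then on arm plus CRRT days. The simulated OSFD had an SD of 3.3 to 4.6, below the planned 5.

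| Scenario (days removed from circulatory / respiratory / renal duration) | No shared severity: unadjusted → adjusted | Strong shared severity: unadjusted → adjusted |
|---|---|---|
| Equal benefit (2.9 / 2.9 / 2.9) | 2.32 → 1.55 | 2.12 → 0.62 |
| Mostly renal (1 / 1 / 5) | 1.39 → 0.47 | 1.31 → −0.91 |
| Renal only (0 / 0 / 4) | 0.60 → −0.12 | 0.56 → −1.22 |
| No effect on CRRT (3.5 / 3.5 / 0) | 1.47 → 1.47 | 1.36 → 1.37 |
| Raises CRRT, helps other organs (3.5 / 3.5 / −2) | 0.36 → 1.24 | 0.34 → 1.60 |
| No effect at all | 0 → 0 | 0 → 0 |

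The unadjusted column is the effect of assignment. Adjustment shrinks it, reverses it, inflates it or leaves it alone, according to how treatment acts on CRRT.

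Renal harm: swapping the arm labels in the renal-only row changes both signs. With strong shared severity, a true loss of 0.56 days is then reported as a gain of 1.22.

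Subgroups: in the renal-only scenario with strong shared severity the overall effect is +0.56, yet it is −0.25 among patients with any CRRT and −1.27 among those without. Both subgroups point the wrong way.

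**4. What attenuation would do to power.** Power = Φ(δ / (5 × √(2/98)) − 1.96), with 5 × √(2/98) = 0.714. The share of the 2-day effect absorbed is assumed. SD is held at 5, although adjustment would also alter the residual SD.

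| Share absorbed | δ (days) | Power |
|---|---|---|
| 0% | 2.0 | 0.80 |
| 25% | 1.5 | 0.56 |
| 50% | 1.0 | 0.29 |
| 75% | 0.5 | 0.10 |

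At 100% only the 0.05 error rate remains.

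**The case against.** The best defence is that the section defining the primary analysis contains none of this. Statistical methods names centre alone, its sensitivity analyses concern centre alone, and its subgroups are tied to severity and baseline features. That stands. A reader might infer that the primary model itself removes or reverses the treatment effect; the documents do not support that, because no CRRT or therapy term is assigned to that model. A reader might also infer that subgroups will be formed by concomitant therapy; subgrouping is stated only for CRRT.

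Second, the CRRT sentence gives drug exposure as its purpose, and Table 1 schedules plasma vitamin C on Days 0, 1, 3 and 7 with CRRT recorded on the same days. A pharmacokinetic reading is plausible, but nothing confines the CRRT terms to a concentration model. Nor would the purpose justify an efficacy covariate: study-drug exposure exists only in the active arm, so a CRRT term in a between-arm model of OSFD cannot isolate it.

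Third, some CRRT will already be running at Day 0, since patients enter after more than 48 hours of organ failure. That part is a legitimate baseline variable, but the text does not separate it from later CRRT.

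Fourth, covariate lists often sit in an analysis plan that is not shown. That would answer a complaint about missing detail. Here the article states a rule, and the rule is unsound if applied to efficacy.

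**Conclusion.** The concern holds in a limited form. The article commits to adjustment and subgrouping by CRRT parameters, and to adjustment for concomitant therapies, without restricting either to values fixed before randomisation. Renal replacement therapy is part of OSFD, so any efficacy analysis that follows those statements no longer estimates the effect of assignment. The bias can run either way and is nil only if treatment does not affect the variables concerned.

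Its size cannot be fixed from the documents. The simulated range, from 0.56 turned into −1.22 to 0.34 turned into 1.60, shows what is possible under assumed inputs and is not a forecast for this trial.

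It is not established that the primary estimate is affected. What is established is a conflict between sections that leaves open which estimate will be treated as final.

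**What to change.** Reconcile Intervention, Data collection and management, and Monitoring with Statistical methods by stating that:

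1. efficacy models and subgroups use only variables fixed before randomisation; organ support at Day 0, already in Table 1, is an example;
2. CRRT parameters after randomisation enter only an exploratory or descriptive model of plasma vitamin C concentration;
3. concomitant therapies after randomisation are reported by arm and are not adjusted for, and the reference to confounding is removed.

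The cost is wording in the protocol, and in the analysis plan if it repeats these statements. No new data are needed, and the sample size of 238 does not change.
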